#### 4.2.3 Nonclinical toxicology

In an acute toxicity study, no death was found at the highest dose of 900 mg/kg in rats and 200 mg/kg in dogs. Clinical observations revealed fluffy hair, piloerection, prone position, humped back, decreased activity, loose/soft stools, and perianal feces in rats of the high-dose group. Vomiting, loose stool, or bloody feces were observed in dogs.

In a 13-week repeat-dose long-term toxicity study, death was observed in female rats at 120 mg/kg and dogs at 25 mg/kg. The toxicities of aumolertinib observed in rats and dogs were mainly manifested in the skin, gastrointestinal tract, and eyes, and the analysis showed that toxicities might be mainly secondary to the potent inhibition of EGFR by the drug or related to significant reductions in body weight and/or food intake. These toxicities were reversible after a 4-week recovery period.

Aumolertinib-related toxicities in rats included soft stools, salivary secretion, skin damage, and eye abnormalities. Histopathological findings were mainly observed in the mammary gland and vagina of rats, as well as the tongue, skin, oral cavity, and thymus of dogs. The skin damages observed in rats and dogs were associated with dermal folliculitis, which is consistent with the literature report that EGFR inhibitors could cause skin damage in rodents and humans. The ulcer and inflammatory reactions observed in the tongues of dogs were similar to the adverse reactions caused by tyrosine kinase inhibitors in humans. In addition, changes in the oral mucosa have also been reported in the study with anti-EGFR antibody therapy.

Evident ocular toxicities in rats and dogs, such as conjunctival hyperemia, corneal changes, and other eye abnormalities, have been reported in patients treated with anti-EGFR therapy. Mastatrophism and mucification of the vaginal epithelium were considered reactions secondary to treatment-related changes in food intake and body weight. Thymic involution/atrophy was considered to be caused by stress response. The severely toxic dose in 10% of animals (STD10) was 60 mg/kg/day in female rats and 120 mg/kg/day in male rats, and the highest non-severely toxic dose (HNSTD) in dogs was 10 mg/kg/day.

Both *in vitro* and *in vivo* genotoxicity studies showed negative results, suggesting that aumolertinib did not induce mutations or cause chromosome breakage at relevant concentrations.

The no-observed-adverse-effect level (NOAEL) of aumolertinib on reproduction and early embryonic development was 100 mg/kg/day for male rats and 30 mg/kg/day for female rats. Statistically significant decreases in mean gravid uterus weight, implantation sites, and number of live fetuses were noted in female rats at 100 mg/kg/day. However, no drug-related changes were observed in sperm count, motility, and sperm morphology test in male rats at 100 mg/kg/day. Aumolertinib has no teratogenic effect on rat embryo-fetal development, with a NOAEL of 100 mg/kg/day.

#### 4.2.4 Clinical studies

##### 1) Clinical study of aumolertinib in NSCLC

The IND application for aumolertinib has been approved by the US FDA, TFDA in Taiwan, China, and NMPA in mainland China, respectively. The international multicenter phase I/II clinical studies of second-line treatment in advanced NSCLC patients with EGFR T790M mutations began in 2017, and the multicenter phase III clinical studies of first-line treatment in advanced NSCLC patients with EGFR-sensitive mutations began in 2018. In Mar. 2020, aumolertinib was approved by the CFDA (now NMPA) for the second-line treatment of advanced NSCLC with EGFR-sensitive mutations.

A total of 26 subjects were included in the phase I escalation study of aumolertinib. No dose-limiting toxicity (DLT) was observed in the low-dose group (55/110 mg), and only 1 DLT (Grade 3 anemia) was observed in 6 subjects of the 220 mg dose group, and only 1 DLT (Grade 3 blood creatine phosphokinase increased) was observed in 6 subjects of the 260 mg dose group. No maximal tolerated dose (MTD) was reached in the dose-escalation study. The results of PK study showed that, in patients with advanced NSCLC who had undergone disease progression after previous EGFR TKI therapy, a single oral dose of aumolertinib administered under fasted conditions was rapidly absorbed, the peak plasma concentration was reached at 4.0 h, and the mean elimination half-life of the drug ranged from 31.29 to 35.19 h. The PK parameters of Cmax and AUC0-t of aumolertinib were generally linearly related to dose within the dose range of 55 to 260 mg. The exposure of the active metabolite HAS-719 was about 1/3 of that of the parent drug, and the PK parameters also showed a linear relationship. The time to reach peak concentration of HAS-719 was about 6 h later than that of the parent drug, and the mean elimination half-life ranged from 49.75 to 63.75 h. The data of multi-dose PK studies showed that following aumolertinib was administered once daily (QD) for 7 consecutive days, its plasma concentrations reached steady state, with little accumulation at steady state compared with single-dose administration. Within the dose range from 55 mg to 260 mg, when the steady state was reached following continuous dosing, the exposure of aumolertinib showed a basically linear relationship with the plasma concentration at steady state and AUC.

In terms of treatment response, the overall objective response rate (ORR) was 42.3% and the disease control rate (DCR) was 80.8% in 26 subjects. For subjects with partial response, there were 3 (3/6, 50.0%) and 4 (4/6, 66.7%) in the 55 mg and 110 mg groups, respectively, with a disease control rate of 100%; the ORR was 37.5% and 16.7%, and the DCR was 75.0% and 50.0% in the 220 mg and 260 mg groups, respectively.

The enrollment of T790M mutation-positive population for the phase I extension study of aumolertinib has been completed, with a total of 94 subjects enrolled in 55 mg (30), 110 mg (33), and 220 mg (31) dose groups. In terms of

safety, common AEs included creatine phosphokinase increased (24.47%), rash (18.09%), cough (18.09%), aspartate aminotransferase increased (13.83%), alanine aminotransferase increased (11.7%), white blood cell count decreased (11.7%), pruritus (11.7%), pain in extremity (14.89%), upper respiratory tract infection (11.7%), urinary tract infection (11.7%), diarrhea (15.96%), back pain (10.64%), and insomnia (10.64%). The overall incidence of AEs was higher in the 220 mg group than that in the 55 mg and 110 mg groups. In terms of treatment response, the overall ORR was 56.4% and the DCR was 91.5% in 94 subjects. Of these, the ORR was 60.0%, 54.5%, and 54.8%, and the DCR was 83.3%, 97.0%, and 93.5%, respectively, in the 55 mg, 110 mg, and 220 mg groups.

In addition, the study showed that food had no significant effect on the PK parameters of aumolertinib and its metabolite HAS-719. For aumolertinib, the time to peak concentration and peak concentration after high-fat meals were not significantly different from those after fasting, but the AUC increased by about 20%; for metabolite HAS-719, the time to peak concentration was prolonged,  $C_{max}$  decreased by about 18%, and the AUC remained the same. Based on the above study results, dosing under fasting conditions or after a meal is recommended in clinical studies.

Based on the safety and efficacy data from the phase I dose escalation and dose expansion studies, in combination with the PK data, the dosing regimen of 110 mg once daily in the phase II dose extension study was determined. A total of 244 subjects were included in the phase II dose extension study of aumolertinib. In terms of efficacy, the ORR was 68.9% (95% CI: 62.6, 74.6), the DCR was 93.4% (95% CI: 89.6, 96.2), and the mPFS was 12.3 months (95% CI: 9.6, 13.8) in 244 subjects. In terms of safety, the 110 mg dose showed good safety and tolerability, and 93.9% of subjects experienced at least one AE. Common AEs (incidence  $\geq 5\%$ ) in the phase II dose extension included blood creatine phosphokinase increased (48, 19.7%), rash (31, 12.7%), aspartate aminotransferase increased (30, 12.3%), alanine aminotransferase increased (28, 11.4%), white blood cell count decreased (27, 11.1%), pruritus (26, 10.7%), anemia (22, 9.0%), diarrhea (18, 7.4%), leukopenia (17, 7%), proteinuria (17, 7%), platelet count decreased (16, 6.5%), and neutrophil count decreased (15, 6.1%). A total of 49 (20.1%) subjects experienced SAEs, of which 13 (5.3%) were related to the investigational medicinal product.

Aumolertinib has a good control effect on brain metastases. The central nervous system (CNS) response assessed by IRC using RECIST v1.1 was summarized as follows: the CNS ORR was 60.9% (95% CI: 38.5%, 80.3%), with one (4.3%) patient in complete response (CR), the CNS DCR was 91.3% (95% CI: 72.0%, 98.9%), the CNS mPFS was 10.8 months, and the CNS mDoR was 11.3 months.

At present, the clinical trials of the third-generation EGFR TKI of the same kind in NSCLC patients with brain metastases are also ongoing. In studies related to osimertinib, the AURA series of clinical trials suggested that, as a second-line treatment, osimertinib had a median PFS of about 7–9 months in subjects with CNS metastases, while the overall PFS was relatively long, about 10–12 months (AURA extension, AURA2, and AURA3). Compared to the traditional first- and second-generation EGFR TKIs, which have a PFS of 9.6 months in the population with CNS metastases, the osimertinib group demonstrated a significant advantage in first-line treatment of brain metastases, with a PFS of 15.2 months (FLAURA).

Based on the above preclinical and clinical data, this study aims to evaluate the efficacy and safety of high-dose aumolertinib as first-line treatment in subjects with EGFR-sensitive mutant advanced NSCLC with brain metastases who have not received any systemic treatment.

### 4.3 Potential Risks and Benefits

#### 4.3.1 Potential risks and control plan

Previous clinical studies of aumolertinib suggested that the changes in gastrointestinal tract and skin reactions as well as laboratory test results should be closely monitored. The following table shows the common and possible adverse reactions in previous clinical trials of aumolertinib.

**Table 1. Common and possible adverse reactions of aumolertinib**

|                               |                                                                                                                                                                                                                                                                                                                                                                                                                                                                                                                                                          |
|-------------------------------|----------------------------------------------------------------------------------------------------------------------------------------------------------------------------------------------------------------------------------------------------------------------------------------------------------------------------------------------------------------------------------------------------------------------------------------------------------------------------------------------------------------------------------------------------------|
| Most common adverse reactions | 
 
Rash: including rash, rash pruritic, macule, rash maculo-papular, papule, rash papular, folliculitis, erythema, erythema nodosum, dermatitis, dermatitis acneiform, blister, urticaria, drug eruption, palmar-plantar erythrodysaesthesia syndrome, and photosensitivity reaction
 
Investigation abnormal: blood creatine phosphokinase increased, aspartate aminotransferase increased, and alanine aminotransferase increased
 
Pruritus: including pruritis and pruritus generalised
 
 |
|-------------------------------|----------------------------------------------------------------------------------------------------------------------------------------------------------------------------------------------------------------------------------------------------------------------------------------------------------------------------------------------------------------------------------------------------------------------------------------------------------------------------------------------------------------------------------------------------------|

|                                                                    |                                                                                                                                                                                                                                                                                                                                                                                                                                                                                                                                                                                                                       |
|--------------------------------------------------------------------|-----------------------------------------------------------------------------------------------------------------------------------------------------------------------------------------------------------------------------------------------------------------------------------------------------------------------------------------------------------------------------------------------------------------------------------------------------------------------------------------------------------------------------------------------------------------------------------------------------------------------|
| Serious adverse reactions                                          | 
 
Possible interstitial lung disease, often manifested as pulmonary interstitial changes, dyspnoea, tachypnoea, cough, or pyrexia
 
Possible heart abnormalities, often manifested as rapid heartbeat, tachypnoea, swelling of ankles and soles, and feeling weak and dizzy
 
                                                                                                                                                                                                                                                                                    |
| Other possible adverse reactions                                   | 
 
Diarrhoea, anaemia, cough, and proteinuria
 
Investigation abnormal: white blood cell count decreased, and neutrophil count decreased
 
Stomatitis: including mouth ulceration, oral mucositis, aphthous ulcer, dry mouth, oral pain, tongue ulceration, and glossodynia
 
Eye and accessory organ disorders: including retinopathy, maculopathy, corneal exfoliation, dry eye, cataract, xerophthalmia, asthenopia, eyelid oedema, blepharochalasis, trichiasis, lacrimation increased, ocular discomfort, and foreign body sensation in eyes
 
 |
| Note: see the Investigator's Brochure for other adverse reactions. |                                                                                                                                                                                                                                                                                                                                                                                                                                                                                                                                                                                                                       |

For the above adverse reactions, the following provisions are made in the protocol to minimize the risk: 1) The safety observation indicators are designed to cover the common adverse reactions of competitors, the changes requiring close attention suggested in the completed preclinical and clinical studies of aumolertinib, as well as the observation of toxicities to the heart, lung, and other vital organs. The termination criteria for subjects and the clinical trial are specified in the protocol. 2) The trial will be conducted in medical institutions with clinical trial qualifications, and experienced investigators will be selected for the clinical trial. 3) During the conduct and implementation of the trial, physicians with rich clinical experience shall regularly pay attention to and examine the health status of the patients and take corresponding treatment measures in time in case of abnormal changes. 4) The safety examinations are completed at the time points defined in the protocol, and AEs occurring in patients outside the hospital are monitored by subject diary, telephone, or in-hospital follow-ups. 5) Additional tests may be performed at any time as deemed necessary by the investigator. In case of any special event after the trial is initiated, if the ethics committee, the clinical physician, or the patient considers it necessary, the study may be immediately halted.

#### 4.3.2 Known potential benefits

Presence of sensitive mutations in EGFR exons 18 to 24 (including exon 19 deletion and L858R mutation) renders NSCLC patients sensitive to EGFR TKI therapy. However, patients treated with the first-generation EGFR TKI will inevitably develop drug resistance in subsequent therapies, with T790M mutation being the leading cause. Aumolertinib, a novel irreversible small molecule inhibitor of EGFR, is able to selectively inhibit EGFR-sensitive mutations and T790M-resistant mutations, while having only minimal inhibitory activity against WT EGFR. Therefore, aumolertinib as first-line treatment for patients with EGFR-sensitive mutant advanced NSCLC with brain metastases may offer the following clinical benefits:

The incidence of brain metastases is approximately 20% to 30% in patients initially diagnosed with NSCLC. As NSCLC progresses, approximately 50% of patients develop brain metastases. First-generation EGFR TKIs have limited efficacy against brain metastases. Aumolertinib could readily penetrate the BBB with a brain-to-plasma exposure ratio > 7. At the same time, aumolertinib not only inhibits EGFR-sensitive mutations, but also inhibits T790M primary mutations and drug resistance mutations. Brain metastases are the most common cause of initial disease progression following first-generation TKI therapy. First-line treatment with aumolertinib has the potential to control, prevent, or delay the occurrence of brain metastases due to its ability to penetrate the blood-brain barrier and inhibit T790M mutations.

Available clinical data have shown that aumolertinib 110 mg as second-line treatment has a good control effect on brain metastases. The CNS response assessed by IRC using RECIST v1.1 was summarized as follows: the CNS ORR was 60.9% (95% CI: 38.5%, 80.3%), the CNS DCR was 91.3% (95% CI: 72.0%, 98.9%), the CNS mPFS was 10.8 months, and the CNS mDoR was 11.3 months. In addition, pharmacokinetic data showed that there was a linear relationship between *in vivo* drug exposure and drug dose within the dose range of 55–220 mg, and the drug was well tolerated in subjects at the highest dose of 220 mg. Therefore, increasing the dose from 110 mg to 165 mg could potentially increase systemic and cerebrospinal fluid exposure, thereby improving the treatment efficacy for brain metastases while remaining safe and tolerable.

Aumolertinib can block the formation of non-selective metabolites through structural optimization, which, coupled with its high selectivity and weak effect on wild-type EGFR, result in less toxic side effects. Current clinical studies have shown that aumolertinib is well tolerated and safe, and its main adverse reactions are changes in gastrointestinal tract, skin, and laboratory tests. The first-line use of aumolertinib can reduce the likelihood and duration of patients being exposed to other TKIs that have relatively significant side effects.

In summary, the available preclinical and efficacy and safety data of aumolertinib in patients with advanced NSCLC indicate that aumolertinib as first-line treatment is expected to have good efficacy and safety in subjects with EGFR-sensitive mutant advanced NSCLC with brain metastases who have not received any systemic treatment at the advanced stage, and high doses may offer potential benefits.

## **5.0 STUDY OBJECTIVES AND ENDPOINTS**

### **5.1 Study Objectives**

#### **5.1.1 Primary objective**

To evaluate the 12-month progression-free survival (PFS) rate of high-dose aumolertinib as first-line treatment of EGFR-sensitive mutant advanced NSCLC with brain metastases.

#### **5.1.2 Secondary objectives**

##### **Secondary study objectives:**

1. To evaluate other anti-tumor efficacy endpoints of high-dose aumolertinib:

Intracranial: intracranial progression-free survival (iPFS), intracranial objective response rate (iORR), intracranial duration of response (iDoR), and intracranial disease control rate (iDCR);

Systemic: objective response rate (ORR), overall survival (OS), duration of response (DoR), and disease control rate (DCR).

2. To evaluate the safety of high-dose aumolertinib.

#### **5.1.3 Exploratory objectives**

To explore the dynamic change of blood gene mapping before and after treatment and its correlation with efficacy.

### **5.2 Study Endpoints**

#### **5.2.1 Efficacy endpoints**

The endpoints of this study will be analyzed based on the tumor response assessment by investigator per RECIST

1.1.

1. Primary endpoint:

12-month PFS rate

2. Secondary endpoints:

Intracranial: iPFS, iORR, iDoR, iDCR

Systemic: ORR, DoR, DCR, OS

#### **5.2.2 Safety endpoints**

Occurrence of AEs; occurrence of SAEs; proportion of subjects withdrawn due to AEs; changes in laboratory tests (blood biochemistry, hematology, and urinalysis); changes in vital signs, physical examination, body weight, 12-lead electrocardiogram (ECG), left ventricular ejection fraction (LVEF), ECOG performance status (PS) score, and ophthalmological examination.

#### **5.2.3 Exploratory endpoints**

**Venous blood:** Dynamic change of blood gene mapping before and after treatment and its correlation with efficacy.

### **5.3 Sample Size**

This is an open-label, multi-center, prospective, single-arm clinical study. The objective is to evaluate the efficacy and safety of high-dose aumolertinib as first-line treatment in patients with EGFR-sensitive mutant advanced NSCLC with brain metastases.

We assumed that the null hypothesis of the 12-month PFS rate was 40%, and the alternative hypothesis was 60%.

With a significance level of 0.1 (two-sided) and a power of 80%, 49 patients were required. Considering a dropout rate of 20%, the study needed to enroll 63 patients.

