| Duration of treatment:
One cycle of study treatment is defined as 4 consecutive weeks of administration. The treatment will continue until progressive disease (if the investigator believes that the patient can continue to benefit clinically from the treatment, the patient can continue to receive the drug even if the progressive disease is present as per RECIST 1.1) or meeting the termination criteria.                                                                                                                                                                                                                                                                                                                                                                                                                                                                                                                                                                                                                     |                                                                 | Study duration:
According to the study design, enrollment is planned to last for 6 months and follow-up 20 months |                                                                                                                                                                                                                                                                                                                                                                                                                                                                  |                  |                  |  |                  |                                                                                                                                                                                                                                                                                                                                                      |                                                                 |  |                                                                                                                                                                                                                                                                                                                                                                                                                                                                  |

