**Sample size calculation:**

This is an open-label, multi-center, prospective, single-arm clinical study. The primary objective is to evaluate the efficacy and safety of high-dose aumolertinib as first-line treatment in patients with EGFR-sensitive mutant advanced NSCLC with brain metastases. We assumed that the null hypothesis of 12-month PFS rate was 40%, and the alternative hypothesis was 60%. With a significance level of 0.1 (two-sided) and a power of 80%, 49 patients were required. Considering a dropout rate of 20%, the study needed to enroll 63 patients.

205

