##### **12.4.2.1 Analysis of primary efficacy endpoint (12-month PFS rate)**

The Kaplan-Meier plot will be generated, and the 12-month PFS rate, median PFS and its 95% CI will be calculated. In addition, the PFS rate at 6, 12, 18, and 24 months will be summarized.

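### The stated inputs (40% vs 60%, two-sided alpha 0.1, 80% power) do not lead to 49 patients; alpha, power and N need to be reconciled

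*Protocol*

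**What the plan says.** Protocol section 5.3 describes the design and the hypotheses: "This is an open-label, multi-center, prospective, single-arm clinical study"; "We assumed that the null hypothesis of the 12-month PFS rate was 40%, and the alternative hypothesis was 60" per cent. It then gives the result: "With a significance level of 0.1 (two-sided) and a power of 80%, 49 patients were required". The sample size paragraph of the synopsis (section 2.0) carries the same figures and adds the inflation step, as does 5.3: "Considering a dropout rate of 20%, the study needed to enroll 63 patients". Neither place names a test, formula, software or critical value.

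The primary analysis in section 12.4.2.1 reads: "The Kaplan-Meier plot will be generated, and the 12-month PFS rate, median PFS and its 95% CI will be calculated". On timing, the synopsis says that "enrollment is planned to last for 6 months and follow-up 20 months", so every patient can be followed past month 12 before the data are cut.

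**The concern.** In a single-arm trial judged against a fixed rate, the null rate, alternative rate, alpha and power determine the sample size once the method is chosen. Here the common methods give clearly fewer than 49 patients, while a different and very common alpha gives exactly 49. At least one of the three printed figures (alpha, power, N) therefore appears to be wrong.

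The false-positive rate is at stake, rather than patient numbers. A two-sided 0.1 test allows 5% in the upper tail, and a two-sided 0.05 test allows 2.5%. The two levels have different cut-offs, so a reader cannot tell from the protocol which standard of evidence the trial was sized for.

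**Working it through.** **Inputs.** From section 5.3: p0 = 0.40, p1 = 0.60, two-sided alpha 0.1 (0.05 in the upper tail), power 80%, stated n = 49, dropout 20%, stated enrolment 63. Normal quantiles: 1.645 (alpha 0.1), 1.960 (alpha 0.05), 0.842 (80% power). The variance p(1−p) is 0.24 under both hypotheses. Because follow-up runs past month 12 for everyone, a binomial calculation is a fair approximation to the Kaplan-Meier rate when losses are few.

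**1. Trying to reproduce 49 at the stated inputs.**

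- Normal approximation: n = [(1.645 + 0.842) × √0.24 / 0.20]² = 37.1, so 38.
- Arcsine: n = [(1.645 + 0.842) / (2 × (arcsin√0.6 − arcsin√0.4))]² = 38.1, so 39.
- Exact binomial (upper tail at most 0.05, smallest n with power at least 80%): n = 42, reject at 23 or more, upper-tail error 0.0375, power 0.803. Power dips to 76.4% at n = 43 and stays at or above 80% from n = 44.

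None of these gives 49.

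**2. Same methods at two-sided 0.05, power 80%.**

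- Normal: [(1.960 + 0.842) × √0.24 / 0.20]² = 47.1, so 48.
- Arcsine: 48.4, so 49.
- Exact binomial: n = 49, reject at 27 or more, upper-tail error 0.0231, power 0.8018.

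Two of the three methods give 49.

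**3. What 49 patients deliver (exact binomial).**

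| Two-sided alpha | Reject at | Upper-tail error | Power at 60% |
|---|---|---|---|
| 0.1 | ≥ 26/49 | 0.0439 | 0.872 |
| 0.05 | ≥ 27/49 | 0.0231 | 0.802 |

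**4. Does the choice of alpha change a verdict?** At 26/49 (53.1%), the standard error is √(0.531 × 0.469 / 49) = 0.0713. The lower limit of the 90% interval is 0.531 − 1.645 × 0.0713 = 41.3% (Wald) or 40.7% (log-log), both above 40%. The lower limit of the 95% interval is 39.1% (Wald) or 38.3% (log-log), both below 40%. The two levels disagree at that count.

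**5. Less common survival-type formulas at the stated inputs.** The protocol names no method, so transformed Kaplan-Meier formulas were also tried at two-sided 0.1 and 80% power:

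| Transform | Null and alternative variance | Null variance only | Alternative variance only |
|---|---|---|---|
| Log | 45 | 57 | 26 |
| Log-log | 37 | 33 | 47 |

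The range is about 26 to 57. It brackets 49, but no variant gives 49.

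**6. Dropout step.** 49 / 0.80 = 61.25, so 62. Enrolling 63 allows 1 − 49/63 = 22.2% dropout, and 63 × 0.80 = 50.4 covers the 49.

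**The case against.** The strongest reply is that the protocol names no method. The transformed Kaplan-Meier formulas spread widely enough to bracket 49. Log-log with the alternative variance reaches 47, and an added assumption of roughly 7–10% loss by month 12 would bring it to 49. That stands as a reason not to assert which figure is wrong. It does not rescue the text as printed: nothing in the protocol points to that formula, and dropout is already added as a separate 20% step.

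A reader might also take the 95% interval in section 12.4.2.1 as proof that 0.05 was meant, or as a second success threshold that conflicts with 0.1. The document does not support this. The interval attaches most naturally to the median, 95% is used throughout the secondary analyses as a descriptive level, and no section makes a 95% limit a success rule. At most it is compatible with 0.05.

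The match at 0.05 also has a weakness. Exact power at that level falls to 76.6% at n = 50 and holds at or above 80% only from n = 55. So 49 is the smallest qualifying size, not a stable one. Software that reports the smallest n would still return it.

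Finally, the mismatch is conservative at the stated alpha: power exceeds 80% and the upper-tail error stays below 5%. This is correct, and it limits the seriousness of the point.

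**Conclusion.** The printed alpha, power and N do not belong together under standard one-sample methods. At two-sided 0.1, 80% power needs 38 to 42 patients, and 49 give about 87% exact power. The likeliest explanation is that the calculation used two-sided 0.05, where 49 is the smallest exact-binomial size. This is an inference, because the protocol alone cannot show which of the three figures is misstated.

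The consequence is limited. It would be tempting to conclude that the trial is underpowered or its type I error inflated; neither follows. With 49 evaluable patients, exact power is at least 80% at either alpha. The practical gap is one patient in the cut-off (26 or 27 of 49) and a nominal one-sided error of 5% or 2.5%. The stated figures should be corrected, but the discrepancy does not threaten the trial's validity. The dropout figure is off by one patient, which is rounding.

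The power and cut-off figures assume 49 patients with known 12-month status. The Kaplan-Meier analysis with censoring will differ slightly.

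**What to change.** Check the sponsor's calculation on file, name the method, and restate the figures consistently in section 5.3 and the synopsis (the sentence also appears in the table of contents). Either:

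- **two-sided 0.05**, 49 evaluable patients, exact binomial power 80.2%, with a 95% interval for the 12-month PFS rate set against 40%; or
- **two-sided 0.1**, 49 evaluable patients, exact binomial power about 87%, with a 90% interval set against 40%.

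Settle this before the primary data are seen, so that the cut-off is not chosen afterwards. In the same edit, either change 63 to 62 or say that 63 allows about 22% dropout.

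The cost is wording only, with no extra patients. If 0.05 is adopted, the protocol should acknowledge that actual power at 49 is 80.2% rather than the 87.2% available at 0.1.
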